### Procedures

This protocol is in accordance with the 2013 Standard Protocol Items: Recommendations for Interventional Trials (SPIRIT) Statement (Fig 2) and the SPIRIT checklist can be found as S1 File.

**Fig 2 pone.0289633.g002:**
[figure not shown]
SPIRIT figure as recommended by 2013 SPIRIT statement.

### Intervention

Standard treatment (ST) arm

Participants will receive a brief smoking cessation intervention based on the ‘5A’ and ‘5R’ models proposed by the World Health Organization. The ‘5A’ model emphasizes five steps: ***A***sking about tobacco use, ***A***dvising smokers to quit, ***A***ssessing their willingness to quit, ***A***ssisting in quitting, and ***A***rranging for follow-up [8]. Accordingly, our trained research assistant (RA) will ask participants about their tobacco use. The RA will then advise them to quit by a strong message: ‘*According to the World Health Organization*, *smoking kills one in every two smokers*. *Quitting smoking is important to protect your health*. *We are here to help you*.*’* The RA will then assess their willingness to quit by asking two questions: *‘Would you like to quit smoking*?*’* and *‘Do you think you can quit smoking successfully*?*’* If the participant replies *‘yes’* to the first question and either *‘yes’* or *‘unsure’* to the second question, they will be considered smokers who are ready to quit, and the RA will assist them to quit using the **STAR** method: ***S***et a quit date within 1 week, ***T***ell people around them about the participant quitting and solicit support, ***A***nticipate challenges to quit attempt, and ***R***emove all tobacco products. Participants who reply either *‘unsure’* or *‘no’* to the first question and *‘no’* to the second question will be considered smokers who are not yet ready to quit and the ‘5R’ model will be applied. This model comprises five components: ***R***elevance, ***R***isks, ***R***ewards, ***R***oadblocks and ***R***epetition. Accordingly, the RA will ask participants to think about how quitting smoking is personally relevant and encourage them to identify the potential risks of smoking and potential rewards of quitting. The RA will then guide participants to think about any roadblocks to quitting and provide corresponding solutions. Finally, the RA will repeat the assessment of their willingness to quit. Lastly, the RA will arrange follow-up with the participants by phone.

Booster intervention

Booster intervention will be given over the phone at 1-week, 1-month, 3-month, and 6-month follow-up, which are the crucial timepoints for booster interventions for smoking cessation [15–20]. During the conversations, the RA will ask participants about their tobacco use. If participants stopped smoking in the past 7 days, the RA will congratulate them on their success and encourage them to continue. If participants are unsuccessful at quitting, the RA will say, *‘Don’t feel disappointed*. *Would you mind telling me the reasons why you continue to smoke*?*’* The RA will provide brief suggestions to participants based on their responses and reinforce the message that quitting is beneficial for their health.

The brief smoking cessation intervention based on the ‘5A’ and ‘5R’ models is standard practice [8] and has been applied frequently in smoking cessation services [15–20].

According to the toolkit for delivering the 5A and 5R brief smoking cessation intervention developed by the World Health Organization [18], total contact time during the intervention, including follow-up, is less than 30 minutes, which is classified as a brief intervention.

#### Integrated Intervention (II) arm

In addition to the brief smoking cessation intervention based on the ‘5A’ and ‘5R’ models, participants will receive brief advice on alcohol use based on the **FRAMES** model, which is a well-established and effective brief intervention for drinking [28]. The acronym is defined as ***F***eedback of personal risk for alcohol use, emphasis on personal ***R***esponsibility for change, clear ***A***dvice to change, ***M***enu of alternative options, ***E***mpathy as a counseling style, and enhancing self-***E***fficacy.

The RA will invite participants to complete the Alcohol Use Disorders Identification Test (AUDIT) and provide personalized feedback accordingly. AUDIT is a simple instrument that was developed by the World Health Organization to identify individuals who are hazardous drinkers or have active alcohol use disorders. In Hong Kong, there is currently no recommended level of alcohol use because the harmful effects of drinking are considered to outweigh any potential health benefits [29]. A longitudinal study of population cohorts from 1990–2016 across 195 countries and territories also concluded that there is no safe level of alcohol consumption [30]. Therefore, the RA will advise participants to achieve zero alcohol consumption, provided they are classified to have low risk according to the AUDIT (scoring 1–7). After providing the personalized feedback stipulated in AUDIT, the RA will emphasize personal responsibility for change by advising, *‘No one can make this choice for you*. *It is really up to you to make a change*.*’* Additionally, the RA will advise participants, ‘*As a trained counsellor*, *I strongly advise you to stop drinking*. *This can benefit your health and increase your chance of smoking abstinence*.*’* If participants agree to stop drinking, the RA will assist them in identifying five strategies for change, e.g. alternating alcoholic drinks with soft drinks. Throughout the process, the RA will establish an empathetic relationship with participants. Moreover, the RA will support participants’ self-efficacy by saying, *‘Many people can successfully stop drinking*. *With appropriate information and our support*, *I am sure that you can do it as well*.*’* The brief advice on alcohol use will take ≤15 minutes to avoid significantly lengthening the intervention [28].

Booster intervention

Participants will receive booster interventions at 1-week, 1-month, 3-month, and 6-month follow-up. In addition to the cessation advice that will be the same as that received by participants in the ST arm, the RA will ask participants about their alcohol use. If participant stopped drinking in the past 7 days (or 30 days for 1-, 3-, and 6-month follow-up), the RA will congratulate them on their success and encourage them to continue. If participants are unsuccessful, the RA will say, *‘Don’t feel disappointed*. *Would you mind telling me the reasons why you continue to drink*?*’* The RA will provide brief suggestions to participants based on their responses and reinforce the message that stopping drinking is good for their health and will help with smoking cessation.

#### Control arm

Participants will be provided with two leaflets designed by Department of Health, Hong Kong, with one for smoking cessation and another for alcohol reduction, and scheduled telephone follow-up similar to the ST group. They will receive the placebo intervention and boosters of the same duration, promoting their fruit and vegetable intake. According to Li et al. [20], this placebo intervention and boosters do not have any intervention effect on the smoking-related outcomes.

### Intervention integrity

Firstly, all interventions will be delivered by the same RA. Secondly, the RA will be a psychology/social science graduate who is equipped with basic counseling skills. Thirdly, the RA will receive a 2-day training workshop delivered by the research team, and pass both written and oral assessments before implementing the intervention. Fourthly, 10% of delivered interventions will be randomly chosen for audio recording. The research team will listen to the audiotapes to ensure that the RA adhered to the protocol. Fifthly, weekly research meetings will be held to monitor progress.

### Outcome

The primary outcomes are feasibility measures: screening rate, eligibility rate, consent rate, randomization rate, attendance rate of intervention, adherence to intervention protocol, retention rate, completion rate, missing data, and adverse events. The secondary outcomes are effect size of II on self-reported and biochemically validated quit rates at 6 months relative to control and ST. These quit rates are the most useful outcomes to show the effectiveness of smoking cessation interventions [21]. Six months was chosen because it is the gold standard follow-up duration for evaluation in smoking cessation trials [4,15–20,31].

### Measurements

Feasibility measures include screening rate (the number of eligible smokers divided by the number of screened people), eligibility rate (the number of eligible smokers divided by the number of screened people), consent rate (the number of eligible smokers who agree to participate divided by the number of eligible smokers), randomization rate (the number of participants who are randomized divided by the number of eligible smokers who consent to participate), attendance rate(the number of participants who complete the intervention divided by the number of participants who are randomized into the treatment arms (ST and II)), adherence to intervention (the number of participants in the two treatment arms who practice the skills learned during the intervention divided by the number of participants in the two treatment arms), retention rate (the number of participants who remain in the study divided by the number of participants randomized), completion rate (the number of participants who complete the questionnaire divided by the number of questionnaires distributed), missing data (the percentage of missing data), and adverse events (unfavorable or unintended events during the study period that were not present at baseline or appear to have worsened since baseline [32]).

The proposed secondary trial outcome is effect size of II on self-reported and biochemically validated quit rates at 6 months relative to control and ST. The self-reported quit rate will be measured using a structured questionnaire designed by our team. The questionnaire will cover six areas: smoking profile (i.e., number of cigarettes smoked per day, age when starting to smoke, years of smoking, and the Fagerstrom test, which is the gold standard test for physical dependence on nicotine) [15–20,31], cessation history (i.e., previous quit attempts, when previous quit attempt was initiated, and duration of abstinence), readiness to quit, self-efficacy to quit, alcohol use, and demographics. Besides the items measuring the fact of participants, which are not possible to have the psychometric properties, the construct reliability coefficient for the Fagerstom test was 0.74 [33]. and the Cronbach’s alpha for measuring alcohol use using the Alcohol Abstinence Self-Efficacy Scale (AASE) was 0.98 [34]. The biochemically validated quit rate will be confirmed by measuring the level of carbon monoxide in expired air (< 4 ppm) and level of cotinine in saliva (< 115 ng/mL) [15–20,31].

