### Data collection

Participants will be recruited from smoking hotspots in Mong Kok. Smoking hotspots are places where many smokers congregate [31]. Mong Kok is one of the most popular places among Hong Kong youth, including young smokers [35]. The RA will approach smokers who smoke in selected smoking hotspots to deliver leaflets containing information of the study. If smokers are willing to participate, the RA will check their eligibility. Eligible smokers will be invited to join. For smokers who are ineligible or refuse participation, the RA will remind them of the health effects of smoking and drinking and refer them to the government’s quit line. The timeline of this study was presented in S2 File.

Data will be collected at baseline, 1 week, 1 month, 3 months, and 6 months, which are data collection timepoints that are commonly used in smoking cessation trials [4,19,20,31]. All participants will complete a structured questionnaire at each timepoints via telephone. Self-reported quitters at 6 months will be invited for biochemical validation.

Participants in the II arm with high (80%–100%) and low (0%–20%) adherence will be purposively selected for one-to-one, 20–30 minutes, semi-structured interviews to further assess the feasibility of II. All interviews will be conducted by the RA in a meeting room of a local university following a semi-structured interview guide and will be audio recorded. Sample size will be determined by data saturation. Based on previous smoking cessation studies [4,16], we expect data saturation to occur after interviewing 30 participants: 15 from the high adherence group and 15 from the low adherence group. As one outcome of this study is to test the feasibility of the II, no incentive will be provided to the participants.

The audit will be conducted by one auditor who was blinded to experimental or control sites. She will regularly audit the overall quality and completeness of the data, examine source documents, interview investigators and coordinators, and confirm that the clinical center has complied with the requirements of the protocol.

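### Screening rate duplicates eligibility rate among the primary feasibility outcomes, and no defined measure counts the smokers approached, so yield per smoker approached is not identified

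*Protocol article*

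**What the plan says.** The Outcome section fixes the status of these measures: "The primary outcomes are feasibility measures: screening rate, eligibility rate, consent rate, randomization rate, attendance rate of intervention", followed by adherence, retention, completion, missing data and adverse events, ten in all. The definitions are in Measurements:

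- Screening, running straight on into eligibility: "screening rate (the number of eligible smokers divided by the number of screened people), eligibility rate (the number of eligible smokers divided" by the same denominator.
- Eligibility in full: "eligibility rate (the number of eligible smokers divided by the number of screened people").
- Consent: "consent rate (the number of eligible smokers who agree to participate divided by the number of eligible smokers").
- Randomization: "randomization rate (the number of participants who are randomized divided by the number of eligible smokers who consent to participate").
- Completion: "completion rate (the number of participants who complete the questionnaire divided by the number of questionnaires distributed").

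Data collection describes the recruitment sequence. The research assistant approaches people smoking at selected hotspots and hands out study leaflets. Then: "If smokers are willing to participate, the RA will check their eligibility. Eligible smokers will be invited to join". Participants are due a questionnaire at baseline, 1 week, 1 month, 3 months and 6 months.

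Study design and objectives lists a recruitment rate where Outcome and Measurements have the consent rate, and does not define it. Data analysis reports all these measures as frequencies and percentages.

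**The concern.** Feasibility is the primary objective, and the Discussion says a full-scale trial will follow from these results. Recruitment is by street approach without incentive. A planner of the later trial will therefore ask how many smokers must be approached to randomize one.

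That question needs a count of people approached. By its name, the screening rate is the natural place for it, but the definition printed there is that of the eligibility rate. The consent rate does not fill the gap. Anyone who declines on receiving the leaflet is not checked for eligibility and so does not enter its denominator. Read without that qualification, the consent rate would make the population look more recruitable than it is.

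**Working it through.** The plan states no figure for these rates, so there is nothing to reproduce. The check is what the definitions identify.

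**Notation.** A = approached, S = screened, E = eligible, C = consented, R = randomized.

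**Step 1: the measures as written (Measurements).** Screening = E/S; eligibility = E/S; consent = C/E; randomization = R/C. The first two are identical whatever the data.

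**Step 2: what the rates identify together.** (E/S) × (C/E) × (R/C) = R/S, so randomized per person screened can be recovered. The quantity R/A = (S/A) × (R/S) also needs S/A, and A appears in none of the definitions.

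**Step 3: direction of the consent rate.** Let D be the smokers who would have been eligible but declined before the check. Acceptance among all eligible smokers approached is C/(E + D). This is below C/E whenever D > 0. Nobody who declines early is assessed, so D is not observed and the size of the difference is unknown.

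**Step 4: illustration.** R = 150 is the planned sample size (Sample section). The other counts are assumptions made only to show the range: S = 250, E = 180, C = 155.

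- Screening as written = eligibility = 180/250 = 72.0%
- Consent = 155/180 = 86.1%
- Randomization = 150/155 = 96.8%
- Product R/S = 150/250 = 60%

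| Assumed A | Rates as written | S/A | R/A |
|---|---|---|---|
| 300 | 72.0%, 72.0%, 86.1%, 96.8% | 83.3% | 50% |
| 600 | unchanged | 41.7% | 25% |
| 1500 | unchanged | 16.7% | 10% |

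The reported outcomes are the same in all three rows, while the yield per smoker approached differs fivefold.

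**Step 5: does a different reading of screened help?** The term is not defined. If it meant everyone approached, R/S would be the overall yield. The two rates would still be identical, though, and the eligibility rate would mix unwillingness with ineligibility.

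**Step 6: completion rate.** The numerator counts participants and the denominator counts questionnaires. At one time point each participant has one questionnaire, and the ratio is an ordinary proportion. The text does not say that it is calculated per time point.

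**The case against.** The strongest reply is that this is one drafting slip in a set of descriptive percentages. The article ties no progression threshold to them, and neither the sample size nor the comparison of quit rates depends on them. Agreeing over eligible is a normal definition of consent. Fig 1, the CONSORT diagram, is not shown and may count those approached.

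Much of this stands. The weakness in the consent rate is the unlogged earlier step, not the ratio itself. What the trial will actually record cannot be judged without the figure; the point is confined to the written definitions, which do not use the number approached. It remains that the slip is in a primary outcome and falls at the one step the other measures miss.

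Some stronger readings are tempting, and the documents do not support them:

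- *Recruitment yield cannot be estimated at all.* Randomized over screened follows from the defined rates; only the step from approach to screening is lost.
- *The consent rate will be close to 100% by construction.* Eligible smokers are invited separately after the check, Data collection provides for refusal, and written consent follows an information sheet. A person may accept an eligibility check and still decline a six-month trial.
- *The Discussion's statement that about one quarter of young smokers drink gives an expected eligibility rate.* It is a drinking prevalence. Eligibility also depends on age, language, mental disorder and current cessation treatment, and counts a single drink in 30 days.
- *Completion can never exceed 20%.* That needs all five time points in the denominator (150/750) but not in the numerator. The text does not say this, and its singular wording favours a reading per time point.

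**Conclusion.** The concern holds in limited form. One of the ten primary feasibility outcomes duplicates another as written. The consent rate is conditional on prior willingness and overstates acceptance among smokers approached by an unknown amount. The defined rates identify randomized per person screened but not randomized per smoker approached. The duplication is plain from the text and needs no assumption. The conditional consent rate rests on the sequence in Data collection being followed as described. The 50%, 25% and 10% yields illustrate the range left open and are not estimates for this trial.

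The completion-rate wording is a separate, minor ambiguity about questionnaire return after enrolment and has no bearing on recruitment yield.

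The correction matters because it changes what the pilot can conclude about recruitment, and approaches not counted at the time cannot be reconstructed.

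**What to change.** 1. Define screening rate as number screened / number of smokers approached. The research assistant tallies every smoker approached and every refusal before the eligibility check.
2. Keep eligibility rate as eligible / screened, with screened defined as those whose eligibility was checked.
3. Keep the consent rate, state that it is conditional on prior willingness, and report enrolled / approached beside it. The latter should be labelled a yield, since its denominator includes people who could not have been eligible.
4. Reconcile the recruitment rate in Study design and objectives with the consent rate in Outcome and Measurements, by defining it or removing it.
5. As a wording correction, state completion rate at each time point as questionnaires completed / questionnaires due.

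The cost is a tally sheet, a small field burden and a few revised sentences. Sample size, randomization and the quit-rate analysis are unaffected.

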### Data analysis

The first objective, examining the feasibility of the II will primarily be determined by quantitative data. Qualitative data will be used to further explain the intervention feasibility. Quantitative data will be analyzed using SPSS. Descriptive statistics, i.e. frequency and percentage will be used to report the feasibility measures, including screening rate, eligibility rate, consent rate, randomization rate, attendance rate, adherence to the intervention, retention rate, completion rate, missing data and adverse events. Qualitative data will be analyzed by the traditional text analysis method using content analysis. We will use double data entry and manual checking of frequencies during data cleaning to ensure the data quality. The semi-structured interviews will be immediately transcribed and returned to informants to check for accuracy. Two team members will read the transcripts to obtain a general sense of the interviews and separately identify important statements, which will be merged into themes and subthemes. Discrepancies during analyses will be resolved in research meetings. Findings will be returned to informants for comment. Qualitative results will be reported according to Consolidated Criteria for Reporting Qualitative Research. A coding frame with quotations will be used to present results.

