## Discussion

This study will bridge the gap in the existing literature by determining the feasibility of implementing an integrated smoking cessation and alcohol intervention in young Hong Kong Chinese people. Based on the results of this study, a full-scale RCT will be conducted to further examine the effectiveness of this intervention in this population. If II is found to be effective and feasible in the Hong Kong Chinese context, it may lead to a significant change in the delivery of smoking cessation services across different regions and population. Currently, these services, which include those provided by Youth Quitline [37], focus only on smoking behavior and overlook other unhealthy behaviors, such as drinking. However, numerous surveys have observed that approximately one quarter of young smokers are drinkers. Furthermore, prevalence of drinking is similar in other smokers of different age groups. Previous studies have consistently demonstrated that drinking undermines smokers’ likelihood to attempt quitting smoking or to successfully abstain from smoking; moreover, drinking increases the chance of lapse and relapse. Therefore, we expect that an integrated intervention that combines both smoking cessation and alcohol use will significantly improve abstinence rates of smokers with alcohol drinking. Furthermore, given the multiplicative risks of chronic diseases due to the combined effects of smoking and drinking, simultaneously stopping these two unhealthy behaviors will significantly improve the physical health of smokers. Besides, future studies should expand to include different populations and geographical regions to validate the findings obtained in this study.

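### The primary question is whether II is feasible, but attendance and adherence are defined as rates pooled over ST and II, and the adherence measure cannot supply the bands used to select interviewees

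*Protocol article*

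**What the plan says.** The objective concerns II. The research questions, Study design and objectives, and Data analysis all put it that way, the last stating that "examining the feasibility of the II will primarily be determined by quantitative data". Under Outcome, the feasibility measures are the primary outcomes: "The primary outcomes are feasibility measures: screening rate, eligibility rate, consent rate, randomization rate, attendance rate of intervention, adherence to intervention protocol, retention rate", followed by completion, missing data and adverse events.

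Measurements then sets the definitions:

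- **Attendance** is "the number of participants who complete the intervention divided by the number of participants who are randomized into the treatment arms (ST and II".
- **Adherence** has as its numerator "the number of participants in the two treatment arms who practice the skills learned during the intervention", over all participants in those two arms.
- **Retention** is taken over all randomized participants, and **questionnaire completion** over all questionnaires distributed. Neither is split by arm.

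Data collection uses adherence differently. "Participants in the II arm with high (80%–100%) and low (0%–20%) adherence" are to be chosen purposively for interview, with saturation expected after "30 participants: 15 from the high adherence group and 15 from the low adherence group".

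**The concern.** Two things do not fit together.

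First, the question is about II, but half of the attendance and adherence denominators comes from ST, which the protocol itself describes as standard practice. Good attendance in ST could offset poor attendance in II, or the reverse, and the reported figure would not show it. These are primary outcomes, meant to inform a full-scale trial of II.

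Second, adherence in Measurements classifies each person as practising the skills or not. The interview plan needs a percentage for each person. The qualitative sample therefore cannot be drawn from the adherence outcome as defined, and two different quantities would be reported under one name. A further use of the idea, the research assistant's adherence to protocol in Intervention integrity, makes confusion more likely.

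**Working it through.** **Inputs.** Allocation is 1:1:1 (end of the Introduction). Sample gives 50 per arm, 150 in total and 10% attrition. The total checks: 3 × 50 = 150. The 80% power statement cannot be reproduced, because no effect size is given, but nothing here depends on it. The pooled denominator for attendance and adherence is 50 + 50 = 100.

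**What a pooled rate says about II.** If P of the 100 participants in ST and II attend, the number attending in II lies between max(0, P − 50) and min(50, P).

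| Pooled result | II count, lowest to highest | II rate |
|---|---|---|
| 90/100 | 40 to 50 | 80% to 100% |
| 80/100 | 30 to 50 | 60% to 100% |
| 70/100 | 20 to 50 | 40% to 100% |

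For example, ST 50/50 with II 30/50 and ST 30/50 with II 50/50 both report as 80%. The same bounds apply to adherence.

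**Retention.** With the plan's 10% attrition, 150 × 0.90 = 135 remain and 15 are lost. If all 15 were in II, II retention would be 35/50 = 70%; if none were, it would be 100%. The overall figure is 90% in both cases.

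**Precision after splitting.** Exact (Clopper–Pearson) 95% intervals:

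- II alone, 35/50 (70%): 55.4% to 82.1%
- II alone, 40/50 (80%): 66.3% to 90.0%, width 23.7 points
- II alone, 45/50 (90%): 78.2% to 96.7%
- Pooled, 80/100 (80%): 70.8% to 87.3%, width 16.5 points

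The pooled interval is narrower, but it describes a mixture of two interventions.

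**Adherence, the two sections side by side.** In Measurements a participant either counts or does not, and the result is a group proportion. In Data collection each II participant has a value on a 0–100% scale, with bands at the two ends. If yes is scored as 100% and no as 0%, everyone falls into one of the two bands and there is no middle to exclude, so the bands would have no function. They make sense only with a graded individual score, and the text gives none.

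**The case against.** The strongest reply is that this is a matter of tabulation. Arm is recorded for every participant, so II-only rates need no new data. Only attendance and adherence are explicitly pooled over ST and II, while screening, eligibility, consent and randomization precede allocation and are rightly left whole. II is the ST package plus at most 15 minutes of alcohol advice, given by the same research assistant with boosters at the same times, so a large gap between arms is not the likeliest outcome. The two uses of adherence could be reconciled by a scoring rule that a condensed article omits.

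Most of this stands, and it limits the point. The bounds above show what the pooled rate leaves open, not what is expected. The reply does not remove the mismatch, however: the article states the pooled denominators outright, and following them gives a rate that is not the II rate.

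Three stronger readings may tempt a reader, and the documents do not support them.

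- *The feasibility question cannot be answered.* It can be, from data by arm, and the II-only interviews add explanation.
- *Expecting 15 low adherers among 50 (30%) contradicts 10% attrition.* Attrition is loss from the study, and a fully retained participant may practise nothing. The 30 interviews are also an expectation, with the actual number set by data saturation.
- *Any result would count as feasible, because* "Based on the results of this study, a full-scale RCT will be conducted". That Discussion sentence is tied to the results, and the next one is conditional on II being found effective and feasible. Numeric progression criteria are something a condensed article may leave to the full protocol, and the documents give no basis for particular go, amend or stop values.

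**Conclusion.** The point holds as a mismatch between the primary objective and the stated definitions. Attendance and adherence as written estimate a mixture of ST and II, and overall retention adds the control arm. With 50 per arm, a pooled 80% leaves the II rate anywhere between 60% and 100%, and an overall retention of 90% leaves II retention between 70% and 100%. These are arithmetic limits that assume only equal arms of 50. In addition, the yes/no adherence measure cannot yield the individual bands on which the interview sample depends.

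The defect lies in the definitions and not in the data, so it is fully correctable. It should be corrected before feasibility results by arm are seen, so that the choice between the pooled and the II rate does not follow the results.

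**What to change.** 1. Report attendance, adherence, retention and questionnaire completion by arm. Name the II-arm figure (n = 50, with 95% confidence interval) as the primary feasibility result, and keep the pooled rate as supplementary. For the control arm, report whichever of these measures apply to it.
2. Leave screening, eligibility, consent and randomization rates unsplit.
3. Define one adherence score per participant, for example the share of the skills taught to that participant that he or she reports practising. State the cut-off that turns it into the proportion in Measurements, and use the same score for the 0–20% and 80–100% interview bands.
4. Keep this score separate from attendance. A count of contacts completed would largely repeat attendance and, because boosters coincide with follow-up, retention. Give the research assistant's delivery fidelity its own name.

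**Cost.** The tabulation by arm needs no new data. The score needs a short list of the skills taught and a few items asking which were practised. The real price is a wider interval for II alone: about 66–90% for 40/50, against about 71–87% for a pooled 80/100.
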